### Treatment

1.5.

The treatment consists of eight weekly sessions offered in a time period of maximum 12 weeks.^1^ In the first session, therapist and client introduce themselves, share expectations regarding the treatment, and the participant is invited to share the story about the deceased loved one(s). Social support is the central theme of the second session. The client is asked to invite a relative to join the client in this session. During sessions 3, 4, and 5, EMDR is offered. Sessions 6, 7, and 8 consist of changing maladaptive thoughts using conventional cognitive restructuring procedures. Each EMDR session has a duration of 90 minutes, all other sessions a duration of 60 minutes. Participants will receive a manual including psycho-education and exercises focused on identifying and altering maladaptive thoughts. Treatments are conducted by licensed therapists, divided over the Netherlands, who have received a one-day training about the treatment protocol. All therapists have ample experience in treating people confronted with traumatic loss (e.g. homicide, suicide, long-term disappearance) and will be supervised by the third, fourth, and fifth author.

### Analyses

1.6.

To test the first hypothesis, analyses of covariance (ANCOVA) will be conducted (Hox, Moerbeek, & van de Schoot, 2010; van Breukelen, 2006). PG, PTS, or depression levels post-treatment or post-waiting will be included as dependent variable, condition as independent variable, and baseline PG, PTS, or depression levels as covariate. To test hypotheses 2 and 3, the T0 data of the participants from the treatment condition will be combined with the T0.1 data of the waiting list control condition (i.e. ‘combined pre-treatment scores’) and condition will be included as covariate. Second, to test to what extent symptom improvement in treatment is related to improvement in possible mechanisms of change (Hypothesis 2), residual gain scores will be calculated for all outcome measures (i.e. PG, PTS, and depression) and possible mechanisms of change (i.e. a sense of unrealness, negative cognitions, avoidance behaviour, and intrusive memories), following previous work of van Minnen, Arntz, and Keijsers (2002) and Boelen, de Keijser, van den Hout, and van den Bout (2011). As recommended by Steketee and Chambless (1992), residual gain scores will be calculated by subtracting the standardized combined pre-treatment scores multiplied by the correlation between standardized combined pre-treatment scores and standardized post-treatment (or follow-up measures) scores from standardized post-treatment scores (or follow up measures). Multiple regression analyses will be conducted to examine the associations between residual gain scores of PG, PTS, or depression on the one hand and residual gain scores of a sense of unrealness, negative cognitions, avoidance behaviour, or intrusive memories on the other hand, while controlling for condition (i.e. immediate vs. delayed treatment). Third, long-term treatment effects (i.e. 12 and 24 weeks post-treatment) on the three outcome measures will be examined by including Time (dummy coded with the first measurement occasion as reference category) as main effect in multilevel models (Hypothesis 3). Finally, a multilevel analysis with Time (dummy coded with the first measurement occasion as reference category) as main effect will also be conducted to examine change in PG levels during treatment (using B-TG data; Hypothesis 4). In case multiple participants are nested in families of the same deceased person(s) a level will be added to the multilevel analyses. Effect sizes will be computed for change in PG, PTS, and depression levels at all time points. An intention-to-treat principle will be applied during the data analyses.

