## Abstract

**Background**: Confrontation with a traumatic (e.g. disaster-related) loss is a risk factor for the development of psychopathology, including symptoms of prolonged grief (PG), posttraumatic stress (PTS), and depression. Although interventions have been developed for reducing post-loss psychopathology, more research into the effectiveness of treatment is needed to improve care for bereaved persons. Cognitive therapy (CT) and eye movement desensitization and reprocessing (EMDR) have been shown to be effective in trauma-exposed populations. We hypothesize that CT and EMDR are also effective in reducing symptoms among people exposed to traumatic loss.

**Objective**: In this article we describe the rationale of a randomized controlled trial (RCT) to examine (1) treatment effects of CT and EMDR for reducing PG, PTS, and depression among traumatically bereaved people, and (2) the associations between improvements in PG, PTS, and depression symptoms on the one hand and tentative mechanisms of change, including a sense of unrealness, negative cognitions, avoidance behaviour, and intrusive memories, on the other hand.

**Method**: A two-armed (intervention versus waiting list controls) RCT will be conducted. Participants will be asked to fill in questionnaires prior to treatment, during treatment, and one, 12, and 24 weeks post-treatment. Potential participants are people who have lost one or multiple significant other(s) in the Ukrainian plane disaster in 2014 with clinically significant levels of self-rated PG, PTS, and/or depression. Multiple regression, including analysis of covariance, and multilevel regression analyses will be used.

**Discussion**: There is a need for treatment for psychopathology following traumatic loss. Strengths of this study are the development of a treatment that targets grief and trauma-related complaints and the examination of potential mechanisms of change in CT and EMDR. Bereaved people, clinicians, and researchers could benefit from the results of this study.

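### The family level is planned only for the multilevel models (Hypotheses 3 and 4); the Hypothesis 1 ANCOVA and the Hypothesis 2 regressions have no family term

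*Protocol article*

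**What the plan says.** Section 1.6 assigns a method to each hypothesis.

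- **Hypothesis 1:** "To test the first hypothesis, analyses of covariance (ANCOVA) will be conducted". The model has "condition as independent variable, and baseline PG, PTS, or depression levels as covariate" and no other term.
- **Hypothesis 2:** "Multiple regression analyses will be conducted to examine the associations between residual gain scores" of the outcomes and of the possible mechanisms, controlling only for immediate versus delayed treatment.
- **Hypotheses 3 and 4:** multilevel models with Time as main effect.

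The rule on relatives follows: "In case multiple participants are nested in families of the same deceased person(s) a level will be added to the multilevel analyses". The Abstract keeps the two families of methods apart: "Multiple regression, including analysis of covariance, and multilevel regression analyses will be used". ANCOVA therefore belongs with multiple regression, and the rule does not reach Hypotheses 1 and 2.

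Three other sections matter. Participants (1.2) makes family members, spouses, colleagues and friends of the victims eligible. Procedure (1.3) allocates participants, not families, 1:1, with gender, number of losses and type of psychopathology as strata. Sample size (1.7) names the Hypothesis 1 test as the main analysis.

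**The concern.** A rule against dependence between relatives should cover every analysis in which relatives appear together. Here it covers the two uncontrolled analyses of change over time, and omits both the randomised comparison that sizes the trial and the mechanism analysis.

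What is at stake differs between the two omitted analyses. In a regression of one gain score on another, relatives may resemble each other on both variables. Ordinary least squares then counts more independent information than there is, and mechanism associations look firmer than they are. In the randomised comparison the predictor is treatment arm, which individual randomisation makes essentially unrelated to family. The issue there is efficiency, and whether the standard error suits the way relatives happened to be split between the arms.

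**Working it through.** **The plan's own figure.** A two-sample t-test with d = 0.5 (the usual reading of the medium effect in section 1.7), two-sided α = 0.05 and 80% power needs 63.77, so 64 per arm and 128 in total. With 19% dropout, 128 / 0.81 = 158.02. The stated 128 and 158 reproduce, as a calculation for independent observations.

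**Assumed inputs.** The document gives no family size and no ICC. I take m = 2 or 3 participants per family, everyone in such a family, and ICC ρ = 0.1 to 0.5 for the baseline-adjusted quantities.

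**Hypothesis 2.** When predictor and outcome have the same ICC within families, the variance of the slope is understated by the factor

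DE = 1 + (m − 1)ρ²,

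and the true level of a nominal 5% test is 2[1 − Φ(1.96/√DE)].

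| m | ρ | DE | Type I error |
|---|---|---|---|
| 2 | 0.1 | 1 + 0.01 = 1.01 | 5.1% |
| 2 | 0.2 | 1 + 0.04 = 1.04 | 5.5% |
| 2 | 0.3 | 1 + 0.09 = 1.09 | 6.0% |
| 2 | 0.5 | 1 + 0.25 = 1.25 | 8.0% |
| 3 | 0.1 | 1 + 2 × 0.01 = 1.02 | 5.2% |
| 3 | 0.3 | 1 + 2 × 0.09 = 1.18 | 7.1% |
| 3 | 0.5 | 1 + 2 × 0.25 = 1.50 | 11.0% |

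If only half of the participants are in pairs at ρ = 0.3, DE = 1 + 0.5 × 0.09 = 1.045 and the level is 5.5%. A simulation of the regression with a condition term (n = 128, 6,000 runs per setting) agrees with the formula: 5.8% for pairs at ρ = 0.2, 6.7% for pairs at ρ = 0.4, and 8.4% for trios at ρ = 0.4.

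**Hypothesis 1, validity.** I simulated the ANCOVA with relatives individually randomised (n = 128, 6,000 runs, families of 2 or 4, ICC 0.2 to 0.4). Type I error was 4.7% to 5.2%, so there is no inflation on average.

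That average conceals dependence on the realised split. For pairs at ρ = 0.3 the true variance is 1 + 0.3 = 1.3 times the nominal one if every pair shares an arm, and 1 − 0.3 = 0.7 times if every pair is divided. The naive standard error is too small in the first extreme and too large in the second. An actual allocation lies between them.

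**Hypothesis 1, efficiency.** Under individual 1:1 allocation, the variance with a family random intercept relative to ordinary least squares is

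(1 − ρ)(1 + (m − 1)ρ) / (1 + (m − 2)ρ).

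- Pairs: this reduces to 1 − ρ², a cut of 1% (ρ = 0.1), 4% (0.2), 9% (0.3) or 25% (0.5).
- Trios: at ρ = 0.3, 0.7 × 1.6 / 1.3 = 0.86, a cut of 14%. At ρ = 0.5, 0.5 × 2 / 1.5 = 0.67, a cut of 33%.

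**The case against.** **The main analysis is valid as it stands.** This is correct on average. A reader might infer that ignoring families inflates the false-positive rate of the primary test, or that 158 participants are too few. Neither follows. Inflation would need relatives to be allocated together, and section 1.3 describes allocation of participants. For Hypothesis 1 the case rests on precision and on a standard error that fits the actual split.

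**The clusters may hardly exist.** The plan's wording is conditional. Colleagues and friends are eligible too, and clinical-level symptoms are required, so many families may supply one participant. A reader might take the plan to expect several per family, but it does not say so. This objection keeps the low end of each range in play. It does not explain why a conditional rule should cover some analyses and not others.

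**Hypothesis 2 is exploratory.** The introduction presents it as exploring mechanisms, and the Discussion calls it a preliminary evaluation. That limits the weight of the error. The coefficients will still be tested and read.

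**The SAP may deal with it.** For families this is weak, because the article itself states where the adjustment applies. For therapists it is strong. The article says "Treatments are conducted by licensed therapists, divided over the Netherlands" and gives neither their number nor their caseload, and no analysis statement mentions them. A reader might infer that the missing therapist term is a defect that inflates the Hypothesis 1 error rate. That would rest on silence about something an SAP may cover. Its size is also wholly assumed: with clustering in the treated arm only, the variance ratio is [1 + 1 + (m − 1)ICC]/2. This gives 1.025 and about 5.3% type I error for 2 patients per therapist at ICC 0.05, and 1.35 and about 9.2% for 8 patients at ICC 0.10.

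**Conclusion.** The point holds as a stated rule applied incompletely: the plan names family nesting and then leaves it out of the Hypothesis 1 and Hypothesis 2 models.

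- **Hypothesis 2:** standard errors are too small, with type I error from about 5.1% (pairs, ICC 0.1) to 11% (trios, ICC 0.5). At ICC 0.1 to 0.2 in pairs the effect is close to nil.
- **Hypothesis 1:** average type I error stays near 5%. What is lost is 1% to 4% of the variance (pairs, ICC 0.1 to 0.2), rising to 33% (trios, ICC 0.5), together with a standard error matched to the realised split.

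All these sizes rest on assumed family sizes and ICCs, and on every participant belonging to such a family. The document does not support a claim that the primary test is anti-conservative because of families, that the sample size must rise, or that omitting a therapist term is an error.

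**What to change.** Extend the sentence on families in section 1.6 to all four hypotheses.

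- **Hypothesis 1:** fit a linear mixed model with the same fixed effects (condition and baseline score) plus a random intercept for family, defined by the shared victim or victims.
- **Hypothesis 2:** use the same random intercept, or family-clustered standard errors.
- **Data:** record a family identifier for every participant.
- **Optional:** a sensitivity analysis of Hypothesis 1 with a therapist effect in the treated arm only, if the SAP does not already provide one.

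The cost is analysis wording and one data item, with no added participants or visits. Hypothesis 2 intervals will be slightly wider. Small-sample degrees of freedom are needed, because the family variance may be imprecisely estimated if few families contribute more than one person.

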
### Sample size

1.7.

Our sample size calculation is based on the main analysis to test Hypothesis 1. Based on previous grief trials (Currier et al., 2010 and van Denderen et al., in preparation), we expect to find a medium effect size difference between the conditions. With a power of 80% and α of 0.05, a sample size of at least 128 participants (64 per condition) is needed. By taking into account a dropout rate of 19% (based on the mean dropout rate as reported in Currier et al., 2010), a total sample size of at least 158 participants is required.

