We expect that people in the treatment condition (i.e. CT with EMDR) will show larger reduction in PG, PTS, and depression levels compared to people waiting for treatment (i.e. ‘waiting list controls’; Hypothesis 1). Furthermore, we extend prior work by exploring possible mechanisms of change during treatment. We expect that greater reductions in PG, PTS, and depression levels will be related to greater reductions in a sense of unrealness, negative cognitions, avoidance behaviour, and intrusive memories (Hypothesis 2). Additionally, we expect that PG, PTS, and depression levels will decrease from pre-treatment to 12 weeks and 24 weeks post treatment (Hypothesis 3). Finally, at a micro-level, we anticipate that we will observe reductions in grief complaints during treatment based on measurements of these complaints in each treatment session (Hypothesis 4).

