### Procedure

1.3.

After receiving the filled-in baseline questionnaire and signed consent form potential participants will be screened for eligibility based on the inclusion and exclusion criteria. All participants will be randomly allocated to the intervention group or waiting list control group within one week after signing the consent form. An independent researcher carries out the stratified randomization procedure by using a random number generator (www.random.org). An allocation ratio of 1:1 will be applied. Stratification variables are gender, number of losses (i.e. single versus multiple), and the type of psychopathology that are present at clinical levels (PGD, PTSD, or depression versus comorbidity of these disorders). The results of the randomization will be communicated by e-mail or letter (depending on the way the questionnaire is delivered). Participants voluntarily withdrawing from the treatment will receive questionnaires at each measurement occasion. The costs that are related to the treatment (i.e. therapy costs and travel expenses) will be fully reimbursed by the Victim Fund.

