## Discussion

2.

The loss of one or more significant other(s) due to a manmade disaster is a unique type of traumatic loss. Being confronted with traumatic loss is associated with a higher risk for developing long-lasting psychological complaints, including PGD, PTS, and depression, compared with non-violent losses (e.g. illness; Boelen et al., 2015; Kaltman & Bonanno, 2003; Kloep et al., 2014). To the best of our knowledge, controlled clinical trials examining treatment effects or research into possible mechanisms of change in treatment among bereaved people are scarce. The present article describes the rationale of a RCT comparing CT with EMDR to a waiting list control group that aims to evaluate the effectiveness and potential mechanisms of change of treatment.

Strengths of this study are: (1) the inclusion of an intervention as well as a waiting list control group, (2) use of a homogeneous bereaved sample (e.g. same cause and circumstances of the loss), (3) the focus on three outcome measures (tapping symptoms of PGD, PTSD, and depression), (4) the preliminary evaluation of possible mechanisms of change of the treatment, and (5) process-monitoring of changes in PG levels on micro-level using session-by-session assessments. One of the limitations of this study is the reliance on self-report measures, which may overestimate symptom levels (Engelhard et al., 2007). In addition, we will assess baseline data at one time point, which may lead to overestimation of treatment effects due to regression toward the mean of participants with extreme scores (Biglan, Ary, & Wagenaar, 2000). Furthermore, the waiting list controls start with the treatment after 12 weeks of waiting. Therefore, we are only able to compare the treatment condition to the waiting list controls at the one week post-treatment assessment and not at the 12 weeks and 24 weeks follow-up assessments. Accordingly, the potential working mechanisms of change and the outcome variables will be measured concurrently, we will therefore be unable to examine mediation effects (Maxwell & Cole, 2007). Lastly, we will use an outreach method to recruit participants, which may limit the generalizability of future results to treatment-seeking bereaved people in general.

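### Hypothesis 1 covers three equal outcomes, but the sample size serves one unadjusted test on an outcome it does not name, and no success rule is given

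*Protocol article*

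**What the plan says.** The hypotheses at the end of the introduction of the protocol article state Hypothesis 1 as one prediction on three outcomes: treated participants "will show larger reduction in PG, PTS, and depression levels compared to people waiting for treatment".

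Section 1.6 (Analyses) tests it by analysis of covariance with the baseline score as covariate: "PG, PTS, or depression levels post-treatment or post-waiting will be included as dependent variable, condition as independent variable". That is one model per outcome. Table 1 lists the TGI-SR, PCL-5 and QIDS-SR together as outcomes without ranking them. The Discussion counts "the focus on three outcome measures (tapping symptoms of PGD, PTSD, and depression") among the strengths of the study.

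Section 1.7 (Sample size) then refers to a single analysis: "Our sample size calculation is based on the main analysis to test Hypothesis 1". Its effect size is tied to no outcome: "we expect to find a medium effect size difference between the conditions". From this follows "With a power of 80% and α of 0.05, a sample size of at least 128 participants (64 per condition) is needed", raised to 158 for 19% dropout.

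The article contains no primary outcome, no testing order, no multiplicity adjustment, and no rule on whether one or all three results must be significant for Hypothesis 1 to be supported.

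**The concern.** The hypothesis joins the three outcomes with *and*; the analysis section lists them with *or*; the sample size section treats them as one analysis. A reader cannot tell what result would count as support for Hypothesis 1.

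This matters because a split result is plausible. Under section 1.2, people enter with clinical levels of PGD, PTSD and/or depression, and under section 1.4.1 a QIDS-SR score of 6 or more is enough for the depression criterion. Some participants may therefore have little elevation on one or two of the outcomes, and the effect may differ between them. If depression were significant and PG were not, the article would allow that to be reported either as support or as failure, and the choice could be made after the data are seen. The stated error rate and power would then not be those of the claim that is made.

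**Working it through.** **Inputs from the article.** Power 80%, α 0.05, medium effect, 64 per condition, 19% dropout (section 1.7); 1:1 allocation (section 1.3); three outcomes, each with its own ANCOVA (section 1.6).

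**Assumptions, not in the article.** Medium means a standardised difference d = 0.5, the same on each outcome. The correlation r between the three test statistics is equal for all pairs. The introduction says that PG often goes with raised PTS and depression, so r = 0.5 to 0.9 is used as the main range and r = 0 only as a limit. The baseline-to-post correlation ρ is varied.

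**Step 1: reproduce the plan.** A two-sample t-test with d = 0.5, two-sided α = 0.05 and power 0.80 needs 63.8, so 64 per arm and 128 in total. Power at 64 per arm is 80.1%. A one-sided 0.05 test would need 51 per arm. A test at 0.05/3 = 0.0167 would need 86 per arm, 172 in total. So 128 was built on one two-sided test without adjustment. For dropout, 128/(1 − 0.19) = 158.02, which agrees with 158 to the nearest whole number.

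**Step 2: three tests, each at two-sided 0.05, 64 per arm, no covariate.** With independent outcomes, the chance of at least one false positive is 1 − 0.95³ = 14.3%, and power on all three is about 0.801³ = 51%. For correlated outcomes, trivariate normal test statistics were simulated (2,000,000 draws per value of r), with the mean set to give 80% power per test:

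| r | False positive on any of three | Power, any of three | Power, all three |
|---|---|---|---|
| 0.5 | 12.5% | 95% | 61% |
| 0.6 | 11.8% | 94% | 64% |
| 0.7 | 11.0% | 92% | 66% |
| 0.8 | 9.8% | 90% | 69% |
| 0.9 | 8.4% | 87% | 72% |

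The two success rules are alternatives. With any-of-three, the error rate is too high but power exceeds 80%. With all-three, the error rate stays at or below 5% but power is below 80%.

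**Step 3: credit for the baseline covariate.** If d = 0.5 is the unadjusted difference, ANCOVA works with d/√(1 − ρ²). At ρ = 0.5 this is 0.5/√0.75 = 0.577. Here r is the correlation after baseline adjustment.

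| ρ | Power, one outcome at 0.05 | Power, one outcome at 0.0167 | Power, all three, r = 0.5 to 0.9 |
|---|---|---|---|
| 0 | 80% | 66% | 61-72% |
| 0.3 | 84% | 70% | 67-77% |
| 0.5 | 90% | 80% | 78-85% |
| 0.6 | 94% | 86% | 86-91% |

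The covariate changes power only. For a given r, the any-of-three error rate is the same.

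**Step 4: sample size under each rule, no covariate credit.**

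- Primary outcome or fixed order: 128 (158 recruited) stands for the primary or first test.
- 80% power per outcome at 0.05/3: 172 in total; 172/0.81 = 212.3, so 213 recruited.
- 80% power on all three: 178 in total (220 recruited) at r = 0.5, falling to 152 (188) at r = 0.9.

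**The case against.** Five points can be made on the other side.

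1. *The planned test is ANCOVA, so a t-test understates power.* This stands. At ρ = 0.5 the all-three power is about 78-85%, and at ρ = 0.6 it exceeds 80% throughout the main range. But section 1.7 claims no such credit, its figure reproduces without it, and it does not say whether the medium effect is before or after adjustment. Covariate credit also does nothing for the any-of-three error rate.

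2. *The article does not say that each test is run at 0.05.* Correct. It is inferred from the single α in section 1.7 and from 128 reproducing only without adjustment.

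3. *PG, PTS and depression are distinguishable, so three separate claims may each be tested at 5%.* That is a defensible position, and 5% and 80% would then apply to each claim. The article does not take it: it puts the three in one hypothesis and powers that hypothesis.

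4. *A journal article may leave multiplicity to the full protocol or the SAP.* That covers the adjustment method, and its absence alone would be no finding. It does not cover a sample size statement that rests on one main analysis where the preceding section specifies three.

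5. *PG is the natural primary outcome in a grief trial.* A reader might infer this, but the article gives the three equal standing and admits people on any of them. A PG gatekeeper could block the other two claims in a sample partly below threshold on PG.

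A reader might also infer that the trial has both an inflated error rate and short power. It cannot have both, because each belongs to a different success rule.

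**Conclusion.** The point holds in this form: the calculation in section 1.7 is correct for one outcome, but the article does not say which one, and it leaves open what result would support Hypothesis 1.

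Under an any-of-three reading, the false-positive rate is about 8-13% for assumed r of 0.9 down to 0.5, and 14.3% only if the outcomes were independent, which the introduction speaks against. Under an all-three reading, α is held and power is about 61-72% on the article's own no-covariate basis, or about 78-85% if ρ = 0.5. The article gives neither r nor ρ.

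The stronger statement that the trial is underpowered for Hypothesis 1 is not supported. The shortfall arises only under the all-three rule, and it can vanish with a baseline-to-post correlation that the article leaves unstated.

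**What to change.** Before any comparative analysis, make two changes.

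- **Section 1.6:** state either one primary outcome or a fixed testing order, chosen and justified by the sponsor, or Holm across the three outcomes, at two-sided 0.05. If support for Hypothesis 1 is meant to require all three, say so instead.
- **Section 1.7:** state that 80% power with 128 participants (158 recruited) applies to the primary or first-tested outcome only. If Holm or an all-three rule is chosen, restate the power for that rule with the assumed baseline-to-post and between-outcome correlations. Without covariate credit, power for one outcome at α/3, the first Holm step, is 66%. The 61-72% figure should not be entered as the power of the planned ANCOVA, because it gives no covariate credit.

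**Cost.** A few sentences. A primary outcome or fixed order needs no extra participants; its price is that later outcomes can be claimed only after earlier ones succeed. Holm avoids that order, but per-outcome power falls somewhat. Under Holm or an all-three rule, whether 128 still gives 80% depends on the covariate credit the sponsor can justify; the N without it is in the last step of the working.
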